# Adding muscle power exercises to a strength training program for people with patellofemoral pain: protocol of a randomized controlled trial

**DOI:** 10.1186/s13063-021-05748-x

**Published:** 2021-11-06

**Keywords:** Knee, Muscle strength, Exercise therapy, Quality of life

## Abstract

**Background:**

Strong evidence supports the proximal combined with quadriceps strengthening for patellofemoral pain (PFP) rehabilitation. However, most reported rehabilitation programs do not follow specific exercise prescription recommendations or do not provide adequate details for replication in clinical practice. Furthermore, people with PFP have power deficits in hip and knee muscles and it remains unknown whether the addition of power exercises would result in superior or more consistent outcomes. Therefore, this study is designed to verify whether the benefits of a rehabilitation program addressing proximal and knee muscles comprising power and strength exercises are greater than those of a program consisting of strength exercises only.

**Method:**

This study will be a randomized controlled trial that will be conducted at university facilities. A minimum of 74 people with PFP between the ages of 18 and 45 years will be included. The experimental group will engage in a 12-week resistance training program focusing on proximal and knee muscles using power and strength exercises. The control group will engage in a 12-week resistance training program focusing on proximal and knee muscles using strength exercises only. Primary outcomes will be pain intensity and physical function; and secondary outcomes will be kinesiophobia, self-reported improvement, quality of life, peak hip and knee torque, and hip and knee rate of force development. The primary outcomes will be evaluated at baseline, and after 6 weeks, 12 weeks, 3 months, 6 months, and 1 year. The secondary outcomes will be evaluated at baseline and immediately after the interventions. Therapists and participants will not be blinded to group allocation.

**Discussion:**

This randomized clinical trial will investigate if adding power exercises to a progressive resistance training may lead to more consistent outcomes for PFP rehabilitation. The study will provide additional knowledge to support rehabilitation programs for people with PFP.

**Trial registration:**

ClinicalTrials.gov NCT 03985254. Registered on 26 August 2019.

**Supplementary Information:**

The online version contains supplementary material available at 10.1186/s13063-021-05748-x.

## Introduction

Patellofemoral pain (PFP) is characterized by retropatellar and/or peripatellar pain that is aggravated during activities that increase patellofemoral joint loading (e.g., squatting and ascending/descending stairs) [1], with an annual prevalence in the general population of around 22.7% [2]. Although PFP was previously considered as a self-limiting condition, recent studies suggest that alterations and symptoms may persist for several years [3–5]. Chronic pain associated with PFP has a negative impact on an individual´s level of physical activity and quality of life, interfering with work, activities of daily living, and physical exercise [5–7].

Previous studies reported that people with PFP have decreased strength in hip [8, 9] and knee muscles [10, 11]. Additionally, other parameters of hip and knee muscle capacity seem to be altered in people with PFP, such as rate of force development (RFD) and power [12–15]. Therefore, exercise therapy addressing these deficits may be important for PFP rehabilitation. Some studies reported the effects of rehabilitation programs for PFP patients focused on proximal muscles combined with quadriceps strengthening [16–23]. Two systematic reviews concluded that the combination of proximal and quadriceps rehabilitation results in greater benefits on pain intensity and physical function compared to isolated quadriceps rehabilitation [24, 25]. Nowadays, the combination of hip and knee muscles exercises presents the best level of evidence for pain reduction and physical function improvement during PFP rehabilitation [26]. Despite improvements in pain and physical function, the effects of resistance training on other characteristics seen in people with PFP such as kinesiophobia, quality of life, and catastrophization are unclear [27–30].

According to the American College of Sports Medicine (ACSM), to achieve sustained improvements in muscle capacity, specific evidence-based guidelines must be followed, such as load progression, number of sets and repetitions, time to rest, weekly frequency, and duration of this training [31, 32]. In a systematic review conducted by Lack et al. [24], the included studies evaluated the effects of resistance training targeting proximal muscles of people with PFP. After further analysis using the ACSM criteria, the authors concluded that three out of 14 studies actually incorporated protocols which could evoke improvements in muscle strength [18, 21, 22]. However, none of the included studies completely accomplished the ACSM guidelines for structural strength gains (more than 8 weeks), as the protocols lasted 4 [18, 21] to 8 weeks [22]. Additionally, according to Lack et al. [24], only one study included power exercises [33], even though the exercise protocol was not clearly described for replication in clinical practice or research. This is a common issue among PFP randomized controlled trials highlighted in the systematic review by Holden et al. [34]. The systematic review included 38 studies and the authors concluded that exercise prescriptions are poorly described, which prevents them from being implemented in clinical practice.

Although hip and knee strength exercises present the best level of evidence for pain reduction and physical function improvement in people with PFP [24–26], little is known in relation to their long-term effects. To date, only the study by Fukuda et al. [21] investigated the long-term effects of exercise (12 months) and the study reported that hip and knee strength exercises result in greater benefits on pain intensity and physical function compared to quadriceps strengthening alone. However, rehabilitation programs with exercises that correct other muscle capacity deficits, such as muscle power, can result in superior or more persistent benefits than those with only strengthening exercises. More recently, Barton et al. [30] demonstrated that a 12-week progressive resistance training program (hip and knee strength and power exercises) is feasible and is associated with improvements in pain, physical function, and muscle capacity (strength and power) in people with PFP. Nonetheless, it is unknown whether the benefits of a proximal combined with quadriceps rehabilitation comprising power and strength exercises are greater than those of a proximal combined with quadriceps rehabilitation consisting of strength exercises only.

To improve the knowledge regarding the effects of muscle power exercises on PFP rehabilitation, the main aim of the study will be to verify if including power exercises to a strength training program addressing proximal and knee muscles provides better outcomes in relation to intensity pain and physical function, compared to a strength training program only, in the short, medium, and long term in people with PFP. Furthermore, the aim will be to verify whether the proximal combined with quadriceps rehabilitation comprising power and strength exercises will result in superior benefits on kinesiophobia, self-reported improvement, quality of life, and muscle capacity (increased peak hip abduction and extension torque, and peak knee extension torque; increased hip abduction and extension RFD, and knee extension RFD). The hypothesis of the study is that people with PFP undergoing the proximal combined with quadriceps rehabilitation comprising power and strength exercises will improve considerably concerning the evaluated outcomes when compared to people undergoing the proximal combined with quadriceps rehabilitation composed by strength exercises only.

## Methods

### Trial design

This is a randomized controlled trial. The study will be developed in six stages, according to Fig. 1. The baseline assessment will consist of evaluating anthropometric and demographic data, in addition to pain intensity, physical function, kinesiophobia, quality of life, and muscle capacity. After 1 week, the intervention phase will be initiated, which will consist of two different intervention protocols for 12 weeks, according to the group allocation. Six weeks after starting the intervention, the intensity of pain, physical function, kinesiophobia, and quality of life will be assessed. At the end of the intervention protocols, the participants will be evaluated for pain intensity, physical function, kinesiophobia, quality of life, muscle capacity, and self-reported improvement. After 3 months, 6 months, and 1 year, participants will be re-evaluated for pain intensity and physical function through online questionnaires. The lower limb of the affected side will be assessed. In cases of bilateral symptoms, the more painful lower limb will be assessed [12].

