### Outcome measures

Primary outcomes will be pain intensity and physical function, and secondary outcomes will be kinesiophobia, self-reported improvement, quality of life, peak hip and knee torque, and hip and knee rate of force development. The primary outcomes will be evaluated at baseline, and after 6 weeks, 12 weeks, 3 months, 6 months, and 1 year. The secondary outcomes will be evaluated at baseline and immediately after the interventions.

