### Statistical analysis

The intention-to-treat approach will be applied for all analyses [65]. The differences from baseline will be used in the analysis. The effects of intervention on the outcome measures will be assessed by analysis of variance (ANOVA). For pain and physical function (primary outcomes), a 2-by-6 analysis of variance will be used with the groups (STG and PSTG) as the independent factor and time (baseline, 6-week, post intervention, 3-month follow-up, 6-month follow-up, and 12-month follow-up) as the repeated factor. For kinesiophobia (secondary outcome), a 2-by-3 analysis of variance (2 groups and 3 time points) will be used. For quality of life and muscle capacity (hip and knee torque; hip and knee RFD) (secondary outcomes), a 2-by-2 analysis of variance (2 groups and 2 time points) will be used. For GROC outcome (secondary outcomes), the reference criterion of treatment success will be a score of + 6 (much improved) or higher and these data will be presented as a percentage. Moreover, chi-square tests will be performed to compare the percentage of patients who perceived much improvement in each group based on the GROC scale. Separate models will be used for each outcome measure. For significant group-by-time interactions, planned pairwise comparisons with post hoc Bonferroni will be used to determine differences. The mean difference and 95% CI will be also calculated for each comparison. In cases of missing data, the multiple imputation method will be adopted to impute missing values [66], and per-protocol analysis will be also performed. The significance level will be 0.05. All the statistical analysis will be performed using a Statistical Package for the Social Sciences software program (version 20.0, SPSS, Inc., Chicago, IL, USA), and the researcher who will perform the analysis will be blinded to the group allocation. Interim analyses will not be performed. No additional analyses will be performed in the trial.

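### The visit schedules given for kinesiophobia and quality of life contradict each other, and neither fits both of the stated analysis models

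*Protocol article*

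**What the plan says.** All statements are in the protocol article.

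- **Outcome measures** classes both instruments as secondary: "secondary outcomes will be kinesiophobia, self-reported improvement, quality of life, peak hip and knee torque, and hip and knee rate of force development". It then gives one schedule for all of them: "The secondary outcomes will be evaluated at baseline and immediately after the interventions". The Abstract repeats that schedule. No exception is made for any outcome.
- **Trial design** lists the assessments visit by visit. Baseline includes both ("in addition to pain intensity, physical function, kinesiophobia, quality of life, and muscle capacity"). The mid-treatment visit includes both ("Six weeks after starting the intervention, the intensity of pain, physical function, kinesiophobia, and quality of life will be assessed"). The end-of-treatment visit includes both ("the participants will be evaluated for pain intensity, physical function, kinesiophobia, quality of life, muscle capacity, and self-reported improvement").
- **Statistical analysis** treats the two differently. "For kinesiophobia (secondary outcome), a 2-by-3 analysis of variance (2 groups and 3 time points) will be used", whereas quality of life is grouped with torque and rate of force development (RFD): "For quality of life and muscle capacity (hip and knee torque; hip and knee RFD) (secondary outcomes), a 2-by-2 analysis of variance", with two time points. The section also says that no analyses beyond those listed will be done.
- **Self-reported improvement** defines the global rating of change (GROC) relative to the start of the study. It cannot therefore be taken at baseline.
- **Trial status** reports 37 participants through treatment and follow-up, data being entered, and no analysis yet.

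**The concern.** A repeated-measures model needs a defined set of visits. Here two schedules are stated and two models are specified, and no choice of schedule makes everything consistent. If the two-visit schedule governs, the planned kinesiophobia model has no third time point. If the three-visit schedule governs, a quality-of-life score is scheduled but has no stated use.

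The number of visits also determines the test. The plan makes its Bonferroni pairwise comparisons conditional on a significant group-by-time interaction, and both the degrees of freedom of that interaction and the number of comparisons depend on the visit count. Superior benefit on kinesiophobia and on quality of life is a stated aim in the Introduction, so these are planned results and not incidental data.

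**Working it through.** **Step 1. Count the visits per outcome in each place.** BL = baseline, 6w = 6 weeks, Post = end of treatment.

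| Outcome | Trial design | Abstract and Outcome measures | Statistical analysis |
|---|---|---|---|
| Kinesiophobia | 3 (BL, 6w, Post) | 2 (BL, Post) | 3 |
| Quality of life | 3 (BL, 6w, Post) | 2 (BL, Post) | 2 |
| Torque and RFD | 2 (BL, Post) | 2 (BL, Post) | 2 |
| GROC | 1 (Post) | 2 (BL, Post) | no repeated factor (percentage, chi-square) |

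**Step 2. Test each schedule against the models.**

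- Trial design as the schedule: kinesiophobia fits (3 = 3) and torque and RFD fit (2 = 2). Quality of life does not: 3 − 2 = 1 scheduled assessment is outside the model.
- Outcome measures as the schedule: quality of life fits (2 = 2) and torque and RFD fit (2 = 2). Kinesiophobia does not: 3 − 2 = 1 time point is missing. GROC at baseline also conflicts with its own definition.

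Each schedule fails for one of the two outcomes in question, so at least one statement must change whichever schedule is kept.

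**Step 3. What the visit count changes.** The group-by-time interaction has (groups − 1) × (time points − 1) degrees of freedom:

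- 2-by-3: (2 − 1) × (3 − 1) = 2
- 2-by-2: (2 − 1) × (2 − 1) = 1

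**Step 4. What is inferred.** The Statistical analysis section does not name the visits in either model. For quality of life, baseline and end of treatment are inferred from Outcome measures and from the grouping with muscle capacity, which Trial design does not schedule at 6 weeks. For kinesiophobia, the 6-week visit is inferred as the third because Trial design offers no other.

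**Step 5. Is the sample size touched?** It rests on pain alone. With a 2-point difference, SD 2.8, 80% power, alpha 5% (two-sided assumed, as the article does not say) and 15% losses:

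- n = 2 × (1.960 + 0.842)² × 2.8² / 2² = 30.8, rounded up to 31 per group
- 31 / 0.85 = 36.5, rounded up to 37 per group

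This reproduces the stated figure. Nothing in this point alters it.

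**The case against.** The two-visit sentence reads like a summary line and is visibly loose, since it would also put GROC at baseline. For kinesiophobia, the two more specific sections agree on three visits. For quality of life, the Abstract, Outcome measures and Statistical analysis are all compatible with two visits. Trial design alone gives three, and its 6-week entry may be the slip. The participant timeline in Fig. 1, which is not available here, may show the intended schedule. All of this stands, and it limits what can be concluded. It does not remove the contradiction, because a figure cannot make the written statements agree with one another.

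Three stronger readings are tempting and are not supported:

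- *A reader might infer that the 6-week quality-of-life scores are collected and thrown away*, which would be one of two post-baseline measurements. That is true only if Trial design is the schedule in force. If Outcome measures is, those scores do not exist.
- *A reader might infer that visits could be picked after seeing the data.* The analysis section fixes the number of time points for each outcome, the analyst is blinded to allocation, and no analysis had been done. The remaining freedom is small.
- *A reader might infer that the sections prescribe competing analyses.* Trial design and Outcome measures give schedules. Only Statistical analysis gives models, one per outcome.

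It is also fair to say that a baseline-to-end analysis of quality of life is a legitimate choice, and that a schedule mismatch does not by itself require adding a visit to that model.

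**Conclusion.** The inconsistency is established from the text: 3/2/3 visits for kinesiophobia and 3/2/2 for quality of life across Trial design, Outcome measures and Statistical analysis. The blanket two-visit sentence is wrong as written if the kinesiophobia model is to be run, and it is wrong for GROC in any case. For quality of life, the documents do not show which statement is in error, so any loss of 6-week data is conditional on Trial design being the operative schedule.

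The effect is confined to secondary outcomes. The primary outcomes have the same six assessments in every section, and the sample size is unaffected. The point should be corrected before analysis, but it does not threaten the trial's main conclusion.

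**What to change.** Reconcile the Abstract, Trial design, Outcome measures and Statistical analysis sections before any analysis.

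1. Replace the blanket sentence in the Abstract and Outcome measures with a schedule by outcome: kinesiophobia at baseline, 6 weeks and post intervention; torque and RFD at baseline and post intervention; GROC post intervention only.
2. State whether quality of life is collected at 6 weeks. If it is, list that visit in the corrected schedule and analyse quality of life in the same three-visit model as kinesiophobia. If it is not, delete it from the 6-week visit in Trial design and keep two visits.
3. Name the visits in each model.
4. In either case, adjust for the baseline score and take the post-intervention group contrast as the secondary test. Baseline then enters as a covariate and not as a level of the time factor. This goes beyond reconciling the text, but it uses a score the trial already collects.

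**Cost.** Items 1 and 3 are wording. Item 2 is a matter of fact that the investigators can look up. A three-visit quality-of-life model would be a change to the stated analysis, and it is available only if the score was actually taken. That matters because 37 participants, half of the minimum of 74, had already finished; if they were not asked at 6 weeks, wording cannot supply the data. Item 4 is an analysis specification with no extra data collection. While no analysis has been performed, all of this can be settled without knowledge of results.

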**Fig. 1 Fig1:**
[figure not shown]
Participant timeline: schedule of enrolment, interventions, and assessments

The study will be conducted at the Laboratory of Evaluation and Intervention in Orthopedics and Traumatology (LAIOT) at the Federal University of São Carlos (UFSCar), São Carlos, São Paulo, Brazil, and will follow the CONSORT guideline [35] and the TIDieR checklist to describe the interventions [36]. The present protocol was reported according to the SPIRIT guideline [37].

### Ethics

The research was approved by the University Research Ethics Committee (CAAE: 12417019.8.0000.5504). Each participant will receive explanations regarding research objectives, anonymity of their data, and freedom to participate. Participants will sign an Informed Consent Term (ICT). This study will respect the ethical precepts of Resolution CNS 510/2016 and be performed according to the Declaration of Helsinki. It was registered in ClinicalTrials.gov, on 26 August 2019, under number ID: NCT 03985254.

### Participants and setting

Potential participants will be recruited from the community, gyms, or social media, and a minimum of 74 participants will be included in the study. A researcher will perform a preliminary screening of the eligibility criteria and will explain the study procedures during a telephone call. If the potential participants likely fulfill the inclusion criteria and declare their agreement to participate, the diagnosis of PFP will be confirmed by a physiotherapist through a physical examination [38]. This physiotherapist ([name]) will explain the study procedures and will obtain written consent from patients willing to participate in the trial.

To be included, the participants should meet the following inclusion criteria: (i) men and women affected by PFP (unilateral or bilateral) aged between 18 and 45 years; (ii) insidious onset of symptoms unrelated to a traumatic event; (iii) presenting retropatellar or peripatellar pain (3/10 points according to the visual analog scale—VAS) in at least two of the following functional activities: stair negotiation, running, kneeling, squatting, sitting for long periods, or jumping; and (iv) presence of pain for at least 2 months [17]. The exclusion criteria will be history of surgery to the knees; history of injury or pain in the hip; patellar instability; pain on palpation of the patellar tendon, iliotibial band, Hoffa fat, pes anserinus tendons or knee joint line; signs or symptoms of meniscal or ligamentous knee injuries; presence of Osgood-Schlatter or Sinding-Larsen-Johansson syndrome; and any vestibular, neurological, or musculoskeletal alterations that interfere with or contraindicate the measurement procedures of this study [22, 39]. After randomization, the criterion for dropping out will be the participants not attending the assessments (6 weeks, post intervention and follow-ups).

### Sample size

The sample size of this study was calculated considering a statistical power of 80%, alpha of 5%, and an estimated 15% of sample losses. In order to detect a 2-point difference in pain NRS [40] with a standard deviation of 2.8 points [41], a sample size calculation indicated 37 participants in each group.

### Randomization and allocation

All participants who give consent for participation and who fulfill the inclusion criteria will be randomized to the Strength Training Group (STG) or to the Power and Strength Training Group (PSTG) with a 1:1 allocation ratio. Randomization will be performed using consecutively numbered, sealed and opaque envelopes previously prepared and randomly assigned by a random number generator program (www.randomization.com). Allocation concealment will be ensured, since the randomization code will only be released after the participant has been included in the clinical trial. A researcher not involved in the assessment process will perform the randomization and participant allocation to the groups by opening the envelopes after the baseline evaluation. The physiotherapist, responsible for the intervention, will open the envelope and, will find the treatment condition to be conducted in this participant. The researcher responsible for assessments is not allowed to receive information about the group allocation. Thus, randomization will be conducted without any influence of the physiotherapists and researchers responsible for assessments and interventions.

